Participants were encouraged to routinely monitor food intake, calories, and physical activity; to set reasonable short-term goals; formulate specific plans of action to achieve those goals; and to develop reinforcement and social support for carrying out each major element of the plan. Participants were also asked to keep records of servings of fruits and vegetables, servings of low-fat dairy products, and sodium and fat intake. These records were used by participants and interventionists to assess progress. Because this program placed a strong emphasis on increasing moderate-intensity physical activity, interventionists also helped participants determine how best to fit physical activity into their daily lives, taking into account each participant’s initial motivation, current activity patterns, and weekly progress. The goal was to get each participant to engage in 180 minutes per week, or about 25 minutes per day, of moderate physical activity—primarily walking. Participants were asked to record minutes of physical activity each day, as well as hours slept each night. Sleep hygiene was a module added to the original PREMIER intervention when modifications were made for this population. Other modifications included sessions focusing on stress management, advance planning for anticipated episodes of mental illness, empowering participants to engage in discourse with their prescribers regarding their medication and weight-related concerns, and tips on eating healthily on a restricted income.

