**Self-reported measures**				
Age	x			
Gender	x			
Race	x			
Ethnicity	x			
Education level	x	x	x	x
Medicaid status	x	x	x	x
Medicare disability status	x	x	x	x
Marital status	x	x	x	x
Employment status	x	x	x	x
Annual and monthly income	x	x	x	x
Number of individuals supported by income	x	x	x	x
Income source	x	x	x	x
SF-36 general health subscale [47-49]	x	x	x	x
Behavior and Symptom Identification Scale (BASIS-24) [50]	x	x	x	x
Colorado Symptom Index (CSI) [51,52]	x	x	x	x
Self-reported medications^1^	x	x	x	x
Wisconsin Quality of Life Index (W-QLI) [53-55]	x	x	x	x
Patient Activation Measure (PAM) [56]	x	x	x	x
Body Weight, Image and Self-Esteem Evaluation Questionnaire (B-WISE) [57]	x	x	x	x
Social support scales for eating and exercise behavior [58]	x	x	x	x
Exercise confidence questionnaire [59]	x	x	x	x
Eating habits confidence questionnaire [59]	x	x	x	x
Weight outcome expectancies- ideal and goal weight [60,61]	x	x	x	x
7-day physical activity and sleep log [27]	x	x	x	x
7-day fruit and vegetable consumption [62]	x	x	x	x
Self-reported other efforts to lose weight	x	x	x	x

^1^Self-reported medications were also collected at 18 months.

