### Data analysis

#### Effectiveness analyses of primary aims

We will use generalized estimating equations (GEE) [63] to test the effectiveness of the intervention. GEE estimates the population averaged model while accounting for the correlation among observations as a result of having multiple measures from the same person over time. The primary coefficient of interest will be the time by group (control vs. intervention) interaction, which will indicate the degree of differential change across time between the control and intervention groups. We will include age and study site and time-invariant covariates. Use of outcomes-related medications will be included as time-varying covariates (e.g., controlling for metformin usage when testing intervention efficacy on diabetes risk). The GEE models will be based on the normal distribution with identity link, and the working covariance matrix will be specified as exchangeable. An advantage of GEE is that it is able to estimate models when data are incomplete, assuming the data are missing at random and the working covariance matrix is correctly specified [63]. This will allow us to include all participants according to their initial group assignment in the analyses, which is consistent with the intent-to-treat principle.

For every outcome, we will conduct a series of sensitivity analyses by using transformations that improve the normality of the outcome, using a different family and link (e.g., negative binomial with log link) where appropriate, and using an unstructured working covariance matrix.

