Finally, we will also examine between-group differences for various conceptualizations for the primary outcome of weight, including percentage weight change, the proportion of participants who are at or below his or her baseline weight, and the proportion of participants who lose at least 5% and 10% of their baseline weight. These will be computed at all follow-up timepoints. These are not intent-to-treat results, as these computations require that data are not missing in order to compute the necessary change scores for deriving these different measures of weight. We will test the difference in percentage weight change between the intervention and control groups using a one-way ANCOVA, and test whether the proportion of participants who are at or below their baseline weight at follow-up is different between the arms using multiple logistic regression. We will include age, site, and medications that are known to affect weight as covariates in all analyses.

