### Baseline characteristics

A total of 200 individuals with serious mental illnesses were randomized to one of the treatment arms. Two participants became ineligible after randomization, one due to pregnancy and one due to an unspecified but serious health problem that caused repeated vomiting and resulted in a significant weight loss. At baseline (Table 2), participant diagnoses were affective psychosis (38%), bipolar disorder (32%), schizophrenia spectrum disorders (29%) and PTSD (2%). Participants were taking an average of 3.2 psychiatric medications and 91% were taking an atypical antipsychotic medication. Study participants were an average age of 47.1 (SD = 10.7) years old. Thirty percent were currently working and 35% reported being disabled. About 31% of the sample had a high school diploma, GED or less, and 43% were married or living with a partner.

**Table 2 T2:** Baseline characteristics of the study participants (N = 200)

**Characteristic**	**n (%)**^ **1** ^
Inclusion diagnosis	
Affective psychosis	75 (38)
Bipolar disorder	63 (32)
Schizophrenia spectrum disorder	58 (29)
Post-traumatic stress disorder	4 (2)
Gender	
Male	56 (28)
Female	144 (72)
Race^2^	
White	171 (88)
Non-white	24 (12)
Hispanic ethnicity	4 (2)
Education	
Less than high school	15 (8)
High school graduate/GED	46 (23)
Some college/technical school	87 (44)
College graduate	37 (19)
Post graduate	15 (8)
Marital status	
Never married	57 (29)
Widowed/Divorced/Separated	57 (29)
Married	69 (34)
Living with partner	17 (9)
Annual household income	
$0 - $9,999	54 (28)
$10,000 - $29,999	58 (30)
$30,000 – $49,999	34 (17)
$50,000 or higher	49 (25)
Number of people supported by income, mean (SD)	2.0 (1.3)
Employment status	
Currently working	59 (30)
Disabled	71 (36)
Retired, unemployed, student, homemaker, temporarily laid off, or other	70 (35)
Atypical antipsychotic medication use	182 (91)
Medications taken that affect weight	
≥1 that cause slight/moderate weight loss	77 (39)
≥1 that do not affect weight	168 (84)
≥1 that cause slight/moderate weight gain	21 (11)
≥1 that cause severe weight gain	128 (64)
Mood stabilizer medication use	97 (49)
Anti-depressant medication use	33 (17)
Smoked in the past year	65 (33)
Self-reported diabetes diagnosis	
No	145 (73)
Yes	48 (24)
Don’t know	7 (4)
Self-reported hypertension diagnosis	
No	114 (57)
Yes	70 (35)
Don’t know	15 (8)

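### The primary model adjusts for medication use measured after randomisation, so its time-by-group coefficient need not equal the total effect of assignment

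*Protocol article*

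**What the plan says.** The primary aims (Methods/design) are to test whether the intervention is more effective than usual care on weight and BMI, insulin measures and cholesterol at 6, 12 and 24 months.

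Under Effectiveness analyses of primary aims, each outcome is analysed by a GEE with identity link and exchangeable working covariance. "The primary coefficient of interest will be the time by group (control vs. intervention) interaction". Age and site enter as fixed covariates. Medication enters differently: "Use of outcomes-related medications will be included as time-varying covariates (e.g., controlling for metformin usage when testing intervention efficacy on diabetes risk".

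Table 1 lists self-reported medications at baseline and at each follow-up visit, and its footnote adds: "Self-reported medications were also collected at 18 months". Among the elements added for this population, the Phase 1 description lists sessions "empowering participants to engage in discourse with their prescribers regarding their medication and weight-related concerns".

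For percentage weight change (ANCOVA) and the proportion at or below baseline weight (logistic regression), the article says: "We will include age, site, and medications that are known to affect weight as covariates in all analyses". It does not say whether these are baseline or follow-up values.

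**The concern.** A covariate measured after randomisation is safe in a treatment comparison only if assignment cannot affect it. Here there are two routes by which medication use is tied to what is being tested.

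- **From assignment to medication.** A participant who has been coached to discuss medication and weight may have a prescription changed. Any weight effect of that change is a consequence of being assigned to the intervention, and the adjustment takes it out of the coefficient.
- **From outcome to medication.** Glucose-lowering or lipid-lowering drugs may be started or stopped in response to earlier laboratory values, and insulin and cholesterol are themselves primary outcomes. Medication at a later visit then carries information about earlier outcomes.

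At stake is what the main result means. The aims ask for the effect of offering the programme compared with usual care. The adjusted coefficient is at best the part of that effect that does not pass through medication. Even that reading requires that medication and outcome share no unmeasured cause; a change in psychiatric state is one plausible candidate.

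**Working it through.** The plan gives no figure for this point, so there is nothing to reproduce. The check is algebra plus an illustration.

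**1. What the two models estimate.** Let δ be the effect of assignment not acting through a drug, β the effect of the drug on weight, and Δ the difference between arms (intervention minus usual care) in the change in drug use since baseline. The total effect is

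T = δ + βΔ.

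With drug use at each visit in the model and no unmeasured common cause, the interaction estimates δ. The discrepancy is βΔ.

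- Δ = 0: no discrepancy.
- β > 0 and Δ < 0 (weight-raising drug, used less in the intervention arm): benefit is lost.
- β < 0 and Δ < 0 (outcome-lowering drug, started more in usual care): βΔ > 0, T is smaller in size than δ, and adjustment enlarges the apparent benefit.

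**2. Illustration for weight.** From Table 2, row "≥1 that cause severe weight gain": 128 of 200, or 64%. Assumed, not in the document: 25% (intervention) versus 10% (usual care) of these come off the drug, and β = 4 kg.

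Δ = −0.64 × (0.25 − 0.10) = −0.096; βΔ = 4 × (−0.096) = −0.38 kg.

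A simulation on these assumptions (100 per arm, exchangeable GEE) gave these interactions in kg:

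| Month | Baseline medication | Time-varying medication | Difference | Share of effect |
|---|---|---|---|---|
| 6 | −3.87 | −3.51 | 0.36 | 9% |
| 12 | −3.02 | −2.66 | 0.36 | 12% |
| 24 | −2.01 | −1.65 | 0.36 | 18% |

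The Power analysis and the mean baseline weight of 107.7 kg give a second yardstick. The planned differences are 5.9 − 1.6 = 4.3, 4.4 − 1.6 = 2.8 and 3.6 − 1.8 = 1.8 percentage points, or about 4.6, 3.0 and 1.9 kg. Against these, 0.38 kg is about 8%, 13% and 20%.

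**3. Range.** With β = 4 kg, a 5-point switching gap gives 4 × 0.64 × 0.05 = 0.13 kg and a 25-point gap gives 4 × 0.64 × 0.25 = 0.64 kg.

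A second simulation worked in points of weight, with assumed δ = −2 and β = 2 to 4. It lowered use in the intervention arm by 0 to 30 percentage points from 64%.

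| Drop in use | Share lost | Share lost, with an unmeasured common cause |
|---|---|---|
| 0 | about 0% | about 0% |
| 10 points | 9–17% | 4–12% |
| 20 points | 18–25% | 7–21% |
| 30 points | 26–38% | 10–28% |

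The algebra agrees up to simulation error: for example, at 30 points and β = 4, 1.2/3.2 = 38%. In that same setting with the common cause, the true total was −3.2 and δ was −2. The unadjusted model gave −3.24 and the adjusted one −2.32, which matches neither the total nor δ.

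**4. Working covariance.** With a non-independence working covariance, GEE is consistent only if the mean at one visit does not depend on covariates at other visits, given those at that visit. Arm, visit, site and baseline medication are fixed in advance and raise no such problem. Medication that responds to an earlier outcome can break the condition. The planned unstructured alternative shares this weakness. The figures above do not measure this component: the 0.36 kg is accounted for by βΔ.

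**The case against.** Several points on the other side are sound.

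- A reader might infer that the intervention is designed to change drugs. The documents do not support that. The stated mechanism (Tailored lifestyle intervention) is diet, calorie reduction and activity. The Phase 1 text supports only the prompting of a conversation with prescribers. Influence on medication is possible, but not a documented goal.
- A reader might infer that the adjustment necessarily shrinks the effect. It need not: step 1 shows a case in which it enlarges it.
- A reader might take 0.4 kg as the expected bias. Only the 64% comes from the document; the switching rates and drug effect are assumed. Nothing has been quantified for insulin, glucose or lipids, although the plan's own example is metformin.
- A reader might say that the plan's intent-to-treat statement is false. That statement is narrow. It says that GEE lets the analysis "include all participants according to their initial group assignment in the analyses, which is consistent with the intent-to-treat principle", which concerns who is analysed and in which arm. It does not promise a coefficient free of post-randomisation adjustment.
- A reader might count the ANCOVA and logistic models as the same error. The timing of their medication covariate is not stated and could be baseline. The article also says that those results are not intent-to-treat.
- The listed sensitivity analyses ("For every outcome, we will conduct a series of sensitivity analyses by using transformations that improve the normality of the outcome", other families and links, unstructured covariance) include none without medication. A fuller plan could contain one, so this is not counted as an omission.

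One could also argue that adjustment isolates the lifestyle effect. That is a legitimate question, but a secondary one that needs stronger assumptions. None of these points removes the explicit rule that follow-up medication enters the primary model.

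**Conclusion.** The concern holds in a limited form. The primary coefficient is conditioned on medication use recorded after randomisation, which assignment can affect and which can respond to the outcomes. It therefore need not equal the total effect that the primary aims set out to test, and the exchangeable covariance may add bias if medication follows past outcomes.

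Direction and size cannot be settled from the document. Mediation bias is zero if the arms do not differ in follow-up medication use. Under the assumed 25% versus 10% switching and a 4 kg drug effect, about 0.4 kg of the weight effect is lost. Because the direction is open, the adjustment cannot be defended as conservative. The point rests on a stated rule for the primary model, not on missing detail.

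**What to change.** 1. In the primary GEE, adjust only for medication use at baseline, before randomisation, alongside age and site.
2. Report change in outcome-related medication by arm at each follow-up.
3. Move the time-varying medication model to a labelled sensitivity analysis, fitted with an independence working covariance, and do not interpret it as the total effect.
4. In the ANCOVA and logistic models for weight, state that the medication covariate is the baseline value.

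The cost is a change of wording. Table 1 shows that the data are already collected, and the analysis section is written as work still to be done. The primary estimate would then include any effect that operates through medication changes, which belongs in a comparison with usual care. The independence covariance has its own price in the sensitivity analysis: the article's missing-data argument relies on a correctly specified working covariance, so that model should not carry the main conclusion.

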#### Power analysis of primary aims

We used data from PREMIER DASH diet arm results [30] to estimate power for repeated measures analysis of variance for change in weight. We used repeated measures ANOVA given the lack of well-established methods for estimating power using GEE. Data were available for change at 6 and 18 months. Because reported means and standard deviations were based on completers alone, we adjusted for attrition in our power analyses (although primary analyses will be intent-to-treat). PREMIER reported a 5.9% decrease in weight at 6 months for the DASH diet group and a 1.6% decrease for control (advice only). With an initial total sample size of 280, a 10% (worst case) attrition rate at six months, and alpha level of .05, we have power of .96 to detect a significant group-by-time interaction at 6 months. Using the 18-month values (−1.6% for advice only, -4.4% for DASH) as a conservative estimate for weight change at 12 months, we have power of .87 for the group-by-time interaction term for weight (assuming a 15% worst-case attrition rate). To estimate power at 24 months, we assumed the same rate of weight gain in the DASH group and weight loss from 6 to 18 months in the UC group, consistent with PREMIER. For a 3.6% decrease from baseline in the DASH group and 1.8% decrease for UC at 24 months, we have power of .80 to detect a significant group-by-time interaction at 24 months, assuming 20% attrition. Power for waist circumference, fasting insulin, and insulin sensitivity were based on data reported by Ard [31]. Power for total cholesterol, LDL, and HDL were based on data reported by Obarzanek [64]. Only baseline and 6-month means were available for these variables, so we have computed power to detect a significant group-by-time interaction at 6 months only. For all variables, power exceeds .95 to detect the group-by-time interaction.

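### Percent weight change and the weight-loss proportions are limited to participants with observed follow-up weights, for a reason that is not correct; they can be biased even under the missing-at-random assumption accepted for the GEE

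*Protocol article*

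**What the plan says.** In the protocol article, under Effectiveness analyses of primary aims, weight is tested by a GEE group-by-time interaction. All participants are kept in their assigned group, and the data are assumed missing at random. The sensitivity analyses listed there change the transformation, the family and link, or the working covariance. None changes how missing data are handled.

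The same section then adds further versions of the weight outcome at every follow-up: percent change, the proportion at or below baseline weight, and the proportions losing at least 5% and 10%. Percent change is tested by ANCOVA and the at-or-below-baseline proportion by logistic regression. The covariates are age, site and medications known to affect weight. On the population the article says: "These are not intent-to-treat results, as these computations require that data are not missing in order to compute the necessary change scores".

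The Power analysis section plans for attrition of 10% at 6 months ("a 10% (worst case) attrition rate at six months"), 15% at 12 months ("assuming a 15% worst-case attrition rate") and 20% at 24 months ("assuming 20% attrition"). The Baseline characteristics section gives the number randomised: "A total of 200 individuals with serious mental illnesses were randomized to one of the treatment arms".

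**The concern.** A change score needs a follow-up weight, but that weight need not have been observed. It can be multiply imputed from baseline and any 6- and 12-month weights, and percent change and each yes/no indicator then follow by arithmetic. Nothing about these outcomes forces a completer analysis.

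The choice also fits poorly with the paragraph before it. For weight itself the article accepts MAR so that everyone stays in the analysis. For simple functions of the same weights it drops anyone who missed the visit, together with what was already known about them. A completer model is protected only if dropout depends on nothing beyond the covariates in the model. Earlier follow-up weight is not among those covariates, so dropout that depends on it is MAR for the GEE but a source of bias here.

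At stake are the results that programme planners, whom the trial aims to inform, can read most directly: percent lost and the share who lost 5%.

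**Working it through.** **The plan's own figures.** The stated powers (.96, .87 and .80) cannot be reproduced, because no SD or within-person correlation is given. A two-sample approximation, two-sided alpha .05 and 1:1 allocation assumed, gives the SD each would need: SD = d / [√(2/n) × (1.96 + z_power)], with n = 280 × (1 − attrition) / 2.

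- 6 months: d = 4.3, n = 126, SD = 4.3 / (0.1260 × 3.711) = 9.2
- 12 months: d = 2.8, n = 119, SD = 2.8 / (0.1296 × 3.086) = 7.0
- 24 months: d = 1.8, n = 112, SD = 1.8 / (0.1336 × 2.802) = 4.8

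The point does not rest on these powers. They only suggest an SD range of 5 to 9 points for the illustration.

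**How many are left out.** At 20% attrition, 0.20 × 200 = 40 participants leave each 24-month derived analysis. With equal arms and 20% missing in each, extreme-case bounds on a responder difference are 20 + 20 = 40 percentage points wide.

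**Size of the possible bias.** From the Power analysis section: mean changes of −5.9% and −1.6% at 6 months and −3.6% and −1.8% at 24 months, a true 24-month difference of −1.8 points. Assumed: normal percent change, SD 7, 6-to-24-month correlation ρ = 0.7, everyone weighed at 6 months, and log-odds of later dropout rising by b = 0.10 or 0.15 per point of worse 6-month change. That is an odds ratio of e^0.7 = 2.0 or e^1.05 = 2.9 per SD. This is MAR.

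To first order, the completer mean in an arm with attrition p shifts by −ρ × b × SD² × p. The bias in the difference is therefore about −ρ × SD² × (b_I × p_I − b_C × p_C).

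- Same b, 20% in each arm: 0
- Same b = 0.10, 21.5% intervention and 17.5% usual care: −0.7 × 49 × 0.10 × 0.04 = −0.14
- Same b = 0.10, 25% and 15%: −0.7 × 49 × 0.10 × 0.10 = −0.34
- b = 0.10 in the intervention arm only, 20% in each arm: −0.7 × 49 × 0.10 × 0.20 = −0.69

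Simulation (one million per arm) gives slightly smaller values, because the approximation overshoots as b grows. Paired values are for b = 0.10 and 0.15.

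| Attrition (intervention / usual care) | Dropout related to 6-month change | Completer difference | 5% responder difference (true 9.7 points) |
|---|---|---|---|
| 20% / 20% | neither arm | −1.81 | 9.7 |
| 20% / 20% | both arms, same b | −1.78, −1.80 | 10.0, 10.3 |
| 21.5% / 17.5% | both arms, same b | −1.92, −1.96 | 10.8, 11.1 |
| 25% / 15% | both arms, same b | −2.11, −2.20 | 11.7, 12.4 |
| 20% / 20% | intervention arm only | −2.42, −2.68 | 13.1, 14.5 |

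Regression imputation by arm from the 6-month value gave −1.78 to −1.81 in every row.

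**Range over the SD.** For the intervention-only case the completer difference is −2.15 to −2.27 at SD 5 and −2.81 to −3.15 at SD 9. With the same b in both arms and 21.5% / 17.5% attrition it is −1.87 to −1.88 at SD 5 and −1.99 to −2.08 at SD 9; at 25% / 15% it is −1.95 to −2.02 and −2.26 to −2.39.

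**The case against.** The strongest reply is that these analyses supplement the GEE and that the article openly says they are not intent-to-treat. Both statements are true. No reader is misled about the population, and the main test does not depend on these results. But disclosure does not make the stated reason correct, and it leaves no estimate for everyone randomised.

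A second reply is that imputation detail belongs in a statistical analysis plan. That would hold had the article been silent. Instead it makes a choice and gives an incorrect reason for it.

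Three stronger readings are tempting, and the document supports none of them.

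- **The completer results will overstate the effect, perhaps by half or more.** A ratio of that size (2.68 / 1.80 = 1.5 at SD 7) needs dropout to follow weight in the intervention arm alone. The article reports neither attrition by arm nor any link between dropout and weight. Assessments are separate from group sessions, the 24-month visit falls a year after the programme ends, and the Discussion is positive about retention. Once usual-care dropout follows the same rule, most or all of the bias in percent change goes.
- **The trial is powered on the scale that is analysed in completers.** The percentages are effect-size inputs taken from the earlier trial. Power is stated for the interaction ("we have power of .80 to detect a significant group-by-time interaction at 24 months, assuming 20% attrition"), and the same section says the primary analyses will be intent-to-treat.
- **Missing should simply count as non-response.** That has a bias of its own. With SD 7, a true 5% responder difference of 9.7 points and a dropout odds ratio of 2 per SD of worse 24-month outcome, it gives 8.2, 5.9 and 3.6 points at attrition of 20%/20%, 25%/15% and 30%/10% (intervention/usual care).

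**Conclusion.** The point holds in a limited form. The stated reason for leaving participants out is incorrect, and the completer analyses discard observed weights and can be biased under the article's own MAR assumption. The word is can: direction and size depend on attrition by arm and its relation to weight, neither of which is reported.

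At SD 7 and correlation 0.7, with 20% overall attrition, the bias on a planned 1.8 points is:

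- nil when dropout is unrelated to weight, or when attrition and its relation to weight are equal across arms (the 5% responder difference then moves by at most 0.6 points);
- about 0.1 to 0.3 points when the relation is shared but attrition differs, reaching 0.4 in the steepest case tried;
- about 0.6 to 0.9 points when only intervention-arm dropout follows earlier weight.

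A larger SD widens these figures and a smaller one narrows them. Severity is minor to moderate.

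**What to change.** 1. Delete the statement that the computations require non-missing data.
2. Multiply impute missing weights separately by arm, from all observed weights, baseline covariates and the stratification factors (site, gender, baseline BMI group). If the models adjust for medication at follow-up, include it in the imputation.
3. In each imputed data set derive percent change, at or below baseline, and 5% and 10% loss. Run the planned ANCOVA and logistic models on all randomised participants and pool the results.
4. Keep the completer analysis as a labelled sensitivity analysis. Counting missing as non-response is optional and should be reported with its own bias in mind.

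The cost is a little programming and no new data. The pooled results rely on MAR, as the GEE already does. Participants with no follow-up weight can be imputed only from baseline information, so they add little precision.
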